##### Sample Size

The expected effect size is a 10% reduction in hospital admissions, based on the baseline hospital admission rate of 65.89% in 2024 for the home care program at primary care centers in Tarragona, which belong to the Catalan Health Institute. We assumed a 95% confidence level (alpha error of 5%) and a statistical power of 80%. Additionally, a 15% loss to follow-up was factored into the calculation. With these assumptions, a total of 272 patients per group (control and intervention) will be required. The ARCSINUS approximation (GRANMO Sample Size Calculator v.8.0, available at www.datarus.eu/aplicaciones/granmo/) was used.

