#### 2.3.2. Phase 2: Cluster-Randomized Clinical Trial Across Different Primary Care Centers in Countryside of Tarragona, Spain

A cluster-randomized clinical trial will be carried out for 12 months. The study will be conducted in 20 primary care centers in the Tarragona area. These centers will be randomly allocated into two groups at a ratio of 1:1. The intervention group will have the home care visual map available. No blinding will be implemented in this study. This open-label design is chosen due to the nature of the interventions, which will make blinding unfeasible

This phase of this study will follow the SPIRIT Statement guidelines for reporting clinical trial protocols.

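### The sample size treats patients as individually randomised although 20 centres are randomised, so the stated 80% power does not apply to this design

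*Protocol article*

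**What the plan says.** Section 2.3.2 of the protocol article makes the centre the unit of randomisation: "The study will be conducted in 20 primary care centers in the Tarragona area", and "These centers will be randomly allocated into two groups at a ratio of 1:1". That is 10 centres per arm.

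The Sample Size section then gives its inputs:

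- Effect: "The expected effect size is a 10% reduction in hospital admissions". It does not say whether this is absolute or relative.
- Control rate: a "baseline hospital admission rate of 65.89% in 2024".
- Error rates: "We assumed a 95% confidence level (alpha error of 5%) and a statistical power of 80" per cent.
- Loss: "Additionally, a 15% loss to follow-up was factored into the calculation".
- Method: the arcsine approximation in the GRANMO calculator.

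The result is presented as following from these inputs: "With these assumptions, a total of 272 patients per group (control and intervention) will be required". The section gives no ICC, design effect, number of clusters or cluster size.

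**The concern.** The listed inputs and the method are those for comparing two proportions in independent patients. Patients of one centre share staff, admission habits and access to hospital, so their outcomes are usually correlated. The information in the sample is then less than the headcount suggests. With few centres there is a second limit: more patients per centre cannot remove the variation between centres, and the effective sample per arm can never exceed 10/ICC.

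The 80% power is the stated justification for enrolling 544 frail patients (2 × 272). If real power is near one half or lower, a null result says little about whether the visual map works, yet it would be read against a claim of 80%.

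This is not a detail that a fuller protocol or analysis plan could supply. The article states a calculation, its inputs and its result, and the result does not fit the design described just before it.

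**Working it through.** **Inputs from the protocol article.** Control rate 0.6589; 10% reduction; alpha 5%; power 80%; loss 15%; 272 per group; 20 centres, 1:1.

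**Assumptions of mine.** Two-sided test; the reduction read as 10 percentage points (0.6589 to 0.5589), the more favourable reading for the plan; equal centre sizes; ICC 0.01, 0.02 and 0.05.

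**Step 1: the plan's own figure.** The arcsine formula is n = 2·[(z_α + z_β)/h]², with h = 2·asin√0.6589 − 2·asin√0.5589 = 0.2053.

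n = 2 × [(1.960 + 0.842)/0.2053]² ≈ 372 analysed per group, and 372/0.85 ≈ 438 enrolled.

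The stated 272 is not reproduced. A one-sided test gives about 293, or 345 with loss. A relative 10% (to 59.30%) gives 845, or 994 with loss. All exceed 272. Since a design effect can only raise the number, 272 cannot contain one.

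**Step 2: the loss due to clustering alone.** Start from a correctly sized unclustered trial: 372 analysed per group, so m = 37.2 per centre and power 80% at ICC 0. The design effect is DE = 1 + (m − 1)·ICC, the effective size is n_eff = n/DE, and power = Φ(h·√(n_eff/2) − 1.96).

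| ICC | DE | n_eff per group | Power |
|---|---|---|---|
| 0 | 1.00 | 372 | 80% |
| 0.01 | 1.36 | 273 | 67% |
| 0.02 | 1.72 | 216 | 57% |
| 0.05 | 2.81 | 132 | 39% |

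**Step 3: the trial as planned.** Analysed per group: 272 × 0.85 = 231. Per centre: 272/10 = 27.2 enrolled, 23.1 analysed.

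| ICC | DE | n_eff per group | Power, normal | Power, t with 18 df | Detectable difference at 80%, normal | Same, 18 df |
|---|---|---|---|---|---|---|
| 0 | 1.00 | 231 | 60% | – | 12.8 points | – |
| 0.01 | 1.22 | 189 | 52% | 47% | 14.1 | 14.9 |
| 0.02 | 1.44 | 160 | 45% | 41% | 15.4 | 16.3 |
| 0.05 | 2.11 | 110 | 33% | 30% | 18.6 | 19.7 |

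For example, at ICC 0.02: DE = 1 + 22.1 × 0.02 = 1.44; n_eff = 231/1.44 = 160; power = Φ(0.2053 × √80 − 1.96) = Φ(−0.12) = 45%. The 18-df columns use a noncentral t for a comparison of 10 with 10 centres.

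The first row separates two errors. The fall from 80% to 60% comes from 272 being too small even for independent patients. The further fall, to 52%, 45% or 33%, comes from clustering.

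**Step 4: the ceiling.** As m grows, n_eff tends to 10/ICC. Setting 10/ICC = 372 gives ICC = 0.027. Above that value, no number of patients in ten centres per arm gives 80% power for 10 points. Below it, the numbers needed are large. With ten centres per arm, the required analysed number is 10·n(1 − ICC)/(10 − n·ICC) with n = 372.3. That is 587 analysed (691 enrolled) per group at ICC 0.01, and 1,429 analysed (1,681 enrolled) at ICC 0.02. Section 2.2 gives 3,244 home care users, or 3,244/2 = 1,622 per arm, so at ICC 0.02 the whole programme would fall just short.

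**The case against.** The strongest reply is about size, not direction. The documents give no ICC, so the range is mine. Smaller values hurt less: with 372 analysed per group, power is still 78.6% at ICC 0.001 and 73.2% at 0.005. The Discussion says that similar centres will be selected, and the Data Analysis section plans covariate adjustment; both could reduce variation between centres. The ceiling applies only above 0.027. At 0.01 the pool of 3,244 users could supply the 691 per group needed. It is also fair that part of the shortfall at 272 per group is an arithmetic problem, which is why the ICC = 0 row is shown separately.

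These points limit how far the exact percentages can be pressed. They do not restore the 80%. Any ICC above 0 lowers power, neither the choice of similar centres nor the adjustment is quantified or enters the calculation, and 272 is below the requirement even at ICC 0.

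Nor can the power be recovered by testing without regard to centre. At 23.1 analysed per centre, such a test would have a type I error of about 7.6%, 10.3% and 17.7% at the three ICCs.

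**Conclusion.** The concern holds. The sample size is a calculation for individual randomisation attached to a trial that randomises 20 centres, and the stated 80% power does not describe this trial. Clustering alone would take a properly sized unclustered trial from 80% to between 67% and 39% over ICCs of 0.01 to 0.05. As planned, with 272 enrolled per group, power for a 10-point drop is about 33% to 52%, or 30% to 47% with a test on 18 degrees of freedom.

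These figures assume an absolute 10-point effect, a two-sided test and equal centre sizes. A relative 10% reduction or unequal centres would lower them. The size depends on the assumed ICC; the direction does not.

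**What to change.** 1. From the 2024 records that gave 65.89%, estimate the ICC of 12-month admission across the 20 centres, together with the variation in centre size. Twenty centres give an imprecise estimate, so show a range around it.
2. State the ICC, its source, the expected number of patients per centre, and the design effect 1 + (m − 1)·ICC with a term for unequal centre sizes. Say whether the 10% is absolute or relative and whether the test is two-sided.
3. Restate the power and the minimum detectable difference for 20 centres and 272 per group, using a test that accounts for centre and has few degrees of freedom. Under the ICCs assumed here, the detectable difference is about 14, 15 and 19 points by the normal approximation, or 15, 16 and 20 with 18 df.
4. If 80% is not met, remove the claim, or change the number of patients or centres and justify the new figure. More patients in the same centres help only if the ICC is small.

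The restatement costs one query on existing records, provided that the 2024 data can be split by centre, and one rewritten paragraph. The stated power will look less favourable. Keeping 80% for a 10-point effect would cost more: further consented patients, and possibly further centres.

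### The 272 patients per group do not follow from the stated inputs, which give about 438 (10 points absolute) or 995 (10% relative), so 272 does not deliver 80% power

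*Protocol article*

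**What the plan says.** The Protocol article, section 2.3.2, Sample Size, sets the effect and the baseline together: "The expected effect size is a 10% reduction in hospital admissions, based on the baseline hospital admission rate of 65.89% in 2024". It adds a 5% alpha (expressed as a 95% confidence level), 80% power, and an attrition allowance: "a 15% loss to follow-up was factored into the calculation". The method named is the arcsine approximation in a public sample size calculator. The result is presented as following from these inputs: "With these assumptions, a total of 272 patients per group (control and intervention) will be required".

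Three other places define the calculation. Section 2.3.2 gives equal allocation of the 20 centers: "These centers will be randomly allocated into two groups at a ratio of 1:1". The Variables section makes the main variable a proportion of patients. The Data Analysis section compares groups with a Chi-square test. This is therefore a standard comparison of two proportions, and it can be checked without any outside figure.

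**The concern.** The paragraph gives every number the calculation needs, but the answer is far smaller than those numbers imply. It also leaves open whether the 10% is in percentage points or relative to 65.89%, and that choice more than doubles the sample size.

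This is the only sample size justification in the article, and it concerns the main variable. If the trial stops near 272 per group, it will miss its own target effect much more often than the planned one time in five. A null result could then be read as evidence that the visual map does not work, when the trial was not large enough to show the effect it was planned around.

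**Working it through.** **Inputs** (all from section 2.3.2)
- Control proportion p1 = 0.6589.
- Intervention proportion p2 = 0.5589 if the 10% is absolute, or 0.6589 × 0.9 = 0.5930 if it is relative.
- Alpha 0.05. Sidedness is not stated; two-sided is the natural reading of a 95% confidence level, and one-sided is tried as well.
- Power 0.80, loss 15%, allocation 1:1.

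**Formula.** h = 2·asin(√p1) − 2·asin(√p2); n per group = 2·(z_alpha + z_beta)² / h²; enrolled = n / 0.85.

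**Attempt to reproduce 272, two-sided:** (1.960 + 0.842)² = 7.849.
- Absolute: h = 1.8942 − 1.6889 = 0.2053; n = 2 × 7.849 / 0.04216 = 372.3; / 0.85 = 438.0 (439 if strictly rounded up).
- Relative: h = 1.8942 − 1.7579 = 0.1363; n = 2 × 7.849 / 0.01858 = 845.0; / 0.85 = 994.1, so 995.

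Neither is 272.

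**Other variants tried** (per group)

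| Variant | Absolute: before loss / after loss | Relative: before loss / after loss |
|---|---|---|
| Arcsine, two-sided | 372 / 438 | 845 / 995 |
| Arcsine, one-sided | 293 / 346 | 666 / 784 |
| Pooled normal, two-sided | 373 / 439 | 846 / 996 |
| Continuity-corrected, two-sided | 393 / 463 | 876 / 1031 |
| Arcsine, two-sided, 90% power | 498 / 587 | 1131 / 1331 |
| One-sample arcsine, two-sided | 186 / 220 | 423 / 498 |

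Inflating by 1.15 instead of dividing by 0.85 gives 429 (absolute) or 972 (relative), two-sided. Among the two-group formulas for a 10% reduction, the nearest results are 291 to 294. These need a one-sided test and no loss allowance, and they are still at least 7% above 272. One combination gives 274, but it needs a 10-point *increase*, a one-sided test, a continuity correction and no loss. That contradicts the stated reduction and the stated loss.

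**Power that 272 per group gives.** Analysed after loss: 272 × 0.85 = 231. Power = Φ(h·√(n/2) − z_alpha). For the absolute reading at 231, h·√(231/2) = 2.207, and Φ(2.207 − 1.960) = 0.60. For the relative reading, Φ(1.465 − 1.960) = 0.31.

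| | Absolute 10 points | Relative 10% |
|---|---|---|
| 231 analysed, two-sided | 60% | 31% |
| 272 analysed (no loss), two-sided | 67% | 36% |
| 231 analysed, one-sided | 71% | 43% |
| 272 analysed (no loss), one-sided | 77% | 48% |

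**Detectable difference.** At 231 per group, two-sided, 80% power needs h = 2.802 / √115.5 = 0.261. That corresponds to 65.9% against 53.1%, a drop of about 12.8 points or about 19% relative.

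**Clustering.** Every figure above assumes independent patients. The article gives no intracluster correlation. Assuming 0.01 to 0.05, with 23.1 to 27.2 patients per center (231 or 272 over 10 centers per arm), the design effect 1 + (m − 1)·ICC runs from about 1.2 to 2.3. The finding does not depend on this assumption; clustering only widens the shortfall.

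**The case against.** The arithmetic leaves little room for dispute. The paragraph is intact prose, and it says that 272 follows from its own assumptions, so a fuller protocol or an analysis plan would not remove the disagreement. A finite-population correction using the 3244 home care users comes closest: 293.3 / (1 + 293.3/3244) = 269. But that needs a one-sided test, no allowance for loss and a correction the article never mentions.

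The better objections concern scope, and several stand in part:

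- **More patients could be enrolled.** All program patients are eligible, and 3244 users is about 1622 per arm if evenly split. Both 438 and 995 lie within that pool, before refusals and clustering. This is correct, so the power statement applies to a trial that enrols the stated 272 per group. It does not make 272 the right number.
- **The shortfall differs by reading.** Under the absolute reading, 60% is well below target but is not a negligible chance of success. Only the relative reading (31%) is severe. The two should be kept apart.
- **A one-sided test narrows the gap.** It does, to 71% after loss for the absolute reading, but 80% is not reached even with no loss (77%).
- **The 60% is itself optimistic.** It ignores randomization by center, so it should not be printed as the trial's power without that label.

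**Conclusion.** The concern holds. The stated 272 per group cannot be obtained from the stated inputs. The two-sided arcsine calculation requires 438 enrolled per group (1.6 times 272) for a 10-point drop, or 995 (3.7 times 272) for a 10% relative drop. With 272 enrolled and 15% lost, two-sided power is about 60% or 31%, and the 80% claim fails under both readings of the 10%, one- or two-sided, with or without loss.

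These results rest only on the article's own figures plus the two-sided reading of alpha, with the one-sided alternative shown. They treat patients as independent, so they are the favorable case for a trial that randomizes 20 centers. The unstated meaning of the 10% is a second defect in the same paragraph: it changes the size of the error but does not explain it.

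**What to change.** Rewrite the Sample Size paragraph:

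1. State whether the 10% reduction is absolute (65.89% to 55.89%) or relative (65.89% to 59.30%), and whether alpha is two-sided.
2. Then take one of two routes.
   - If 80% power remains the target, replace 272 with the matching number: 438 (439 rounded up) or 995 per group, stated as before any design effect.
   - If 272 per group is kept, replace the 80% claim with what that number gives after 15% loss: about 60% power (absolute) or 31% (relative), two-sided, and a detectable difference of about 12.8 points at 80% power. Label all of these as ignoring clustering, so that they are not taken as the final power of a cluster trial.

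Correcting the statement costs one paragraph and no extra patients, though the reported power becomes less favorable. Restoring 80% power does need more patients; the program's 3244 users suggest that may be possible, subject to consent and to the design effect.

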##### Recruitment

All patients enrolled in the home care program will be eligible for inclusion in this study. Each patient will receive a brief explanation of the study from the responsible investigator at each center, who will be a healthcare professional. The patients will then be invited to sign an informed consent form. In cases where the patient has significant cognitive impairments, their legal guardian or tutor will be asked to provide consent on their behalf. Patients who do not provide consent will be excluded from this study. This process will ensure clear communication, ethical recruitment, and adherence to consent protocols.

There will be no additional exclusion criteria, as this will be a pragmatic study that will aim to represent the reality of the home care population.

Additionally, we will ensure that the recruitment process reflects the representation of the home care population and that key variables—such as sex, degree of dependency, and socio-economic level—are distributed in a way that is representative of the broader patient population.

##### Variables

The main outcome variables of this study are as follows:The proportion of patients with hospital admissions and avoidable hospital emergency visits (main variable) during the follow-up period.The percentage of patients with ulcers and falls.The total number of avoidable admissions and hospital emergency visits during the follow-up period.The total number of deaths and definitive institutionalizations.Quality of life, measured using the EuroQol-5D index, a record currently available in EMRs [22].

The following are considered as covariates:Age, sex, and socio-economic level [23] and the home care model.Main comorbidities, following the Charlson comorbidity index [24].

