##### Data Analysis

Continuum variables will be described using means and standard deviations if they follow a normal distribution or using means and interquartile ranges otherwise. The normality of the variables will be described using the Kolmogorov test. Categorical variables will be described with percentages and 95% confidence intervals.

Outcomes will be compared between groups using the Chi-square test. A multivariate analysis (Cox regression) will be performed, introducing adjustment variables into the model: socio-demographic variables, risk areas, and covariates, as mentioned before. Covariate selection will be based on clinical relevance and statistical significance (*p* < 0.05 in univariate analysis or established predictors from previous research). The time until the event of the main outcome variables will be considered in the model.

For the “quality of life” outcome, the test scores (averages and percentiles) will be compared between the control and intervention groups at the beginning and at the end of the intervention using the *t* test.

Missing data will be handled under the principle of the worst-case scenario. However, different imputation strategies may be considered depending on the context.

The statistical package R (R foundation for statistical computing, Vienna, Austria; version 4.1.2 or later) will be used for all analyses. Statistical significance shall be established at *p* < 0.05.

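### The blanket Chi-square rule also covers the total of avoidable admissions and emergency visits, a recurrent count that this test does not fit

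*Protocol article*

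**What the plan says.** The Variables section (2.3.2, Phase 2) separates two outcomes built on similar events. One is at patient level and is the main variable: "The proportion of patients with hospital admissions and avoidable hospital emergency visits (main variable) during the follow-up period". The other is a total: "The total number of avoidable admissions and hospital emergency visits during the follow-up period". Listing both indicates that the second is meant as a number of events and not as a number of patients with any event.

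The Data Analysis section then states, without distinguishing types of outcome, "Outcomes will be compared between groups using the Chi-square test". The only outcome given another between-group test is quality of life, compared "at the beginning and at the end of the intervention using the *t* test". The section adds an adjusted Cox regression, of which it says "The time until the event of the main outcome variables will be considered in the model". It names no method for counts or recurrent events.

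**The concern.** A Chi-square test compares how independent units fall into categories. An admission or emergency visit is not an independent unit when one patient can contribute several, and in a frail home care population a few patients may well account for many of the events. If the two arms' event totals are compared by Chi-square, the test takes the variance of a total as equal to its mean. Where patients differ in their underlying risk, the true variance is larger and the p-value too small. A chance excess of frequent attenders in one arm could then be read as an effect of the map at the article's 0.05 threshold.

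A second issue is time at risk. The article expects 15% loss to follow-up and itself counts deaths and definitive institutionalizations as outcomes. Patients will therefore be observed for different lengths of time within the 12 months, and an unadjusted comparison of totals makes no allowance for that.

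**Working it through.** **Plan's own figure.** The article gives no event rate, distribution or power for the count outcome, so there is nothing to reproduce. The stated 272 patients per group concerns the admission proportion and is used below only to set the number of patients.

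**Inputs from the article.** Significance level 0.05 (taken as two-sided); 272 per group less 15% loss, 272 × 0.85 = 231 per arm.

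**Assumed input.** The ratio φ of variance to mean of the per-patient counts.

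**Formula.** Let A and B be the event totals in two arms of n patients, with per-patient mean μ and variance φμ, and no true difference. The Chi-square on totals is (A − B)² / (A + B). Its denominator is about 2nμ, whereas the variance of A − B is 2nφμ. The statistic therefore behaves as φ times a Chi-square variable with one degree of freedom, and

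type I error = 2 × [1 − Φ(1.96 / √φ)].

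| φ | 1.96 / √φ | Type I error |
|---|---|---|
| 1 (Poisson) | 1.96 | 5.0% |
| 1.2 | 1.79 | 7.4% |
| 1.5 | 1.60 | 11.0% |
| 2 | 1.39 | 16.6% |
| 3 | 1.13 | 25.8% |

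**Check by simulation.** 10,000 runs, 231 per arm, no centre effect, Poisson or negative binomial counts. The share of patients with at least one event was set at 0.6589 for illustration only, borrowing the article's "baseline hospital admission rate of 65.89% in 2024". For negative binomial shape k, μ = k × (0.3411^(−1/k) − 1) and φ = 1 + μ/k. Shape 2 gives μ = 1.42 and φ = 1.71; shape 1 gives μ = 1.93 and φ = 2.93.

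| Counts | φ | Chi-square on totals | Patients, any event v none | Patients, 0/1/2/3+ events |
|---|---|---|---|---|
| Poisson | 1.00 | 5.3% | 5.6% | 5.2% |
| Shape 4 | 1.31 | 8.5% | 4.9% | 5.2% |
| Shape 2 | 1.71 | 13.0% | 4.7% | 4.6% |
| Shape 1 | 2.93 | 25.3% | 5.2% | 5.3% |

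The simulated errors on totals agree with the formula (13.4% and 25.2% for the last two rows). A comparison of per-patient means that used the observed between-patient variance stayed at 4.6% to 5.4% on the same data.

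**Sensitivity to the borrowed proportion.** If only 25% of patients have an event, shapes 2, 1 and 0.5 give φ = 1.15, 1.33 and 1.78, and the formula gives 6.8%, 9.0% and 14.2%.

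**What this shows.** The inflation needs two conditions: event totals as the unit of analysis, and φ above 1. When patients are the unit, repeat events do no harm to the error rate, but the hypothesis tested is about the distribution of patients over categories and not about the total number of events.

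**The case against.** - **No sentence assigns the Chi-square to event totals specifically.** The count is reached only through a general sentence. The Variables section also speaks of a total number for deaths and institutionalizations, which occur once per patient and suit a patient-level Chi-square. This stands: the article leaves the unit open. It does not rescue the plan, because the sentence has one exception, the count is not it, and neither unit gives a sound analysis of the total.
- **The Cox regression takes time into account.** This stands in part. A reader might infer that the plan ignores time at risk altogether, and that would be wrong. But as described the model concerns time to event and does not estimate a difference in the number of events.
- **Outcome-specific models are often left to an analysis plan not shown.** That would answer a silence. Here a test is named, and its wording covers an outcome it does not fit.
- **The larger error figures rest on a weak proxy.** This stands. The 65.89% is an admission rate not restricted to avoidable admissions, and the article does not say whether it counts patients or admissions. The shapes are assumed too.
- **The outcome is secondary in weight.** This stands. A reader might infer that the main result is compromised by repeat events. It is not: the main variable is a proportion of patients, for which a patient-level Chi-square suits the data type. Centre clustering is a separate matter.

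**Conclusion.** The mismatch is real: a named test is applied, through a general rule, to a listed main outcome that is a recurrent count. If event totals are compared, the type I error rises from 5% to about 7%, 17% or 26% at assumed variance-to-mean ratios of 1.2, 2 and 3, before any effect of centre. If patients are grouped by count, there is no inflation from repeat events, but the total goes untested and unequal follow-up is ignored.

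It would be tempting to say that the plan will produce too many false positives. The documents do not support this unconditionally, since they fix neither the unit of analysis nor the event distribution, and with Poisson counts there is no inflation. The misfit between test and outcome is firm; the size of the error is conditional. The text should be corrected, but the point does not touch the type of test chosen for the main variable.

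**What to change.** In Data Analysis, restrict the Chi-square, or another test of proportions, to the yes/no outcomes. For the count, add that the number of avoidable admissions and emergency visits per patient will be analysed with a model that allows for overdispersion, such as negative binomial regression or Poisson regression with robust variance. Use log person-time at risk as the offset, and allow for centre with a small-sample correction suited to 20 centres. Report a rate ratio with its 95% confidence interval. State which events end a patient's time at risk.

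The cost is a sentence or two of text and intervals wider than a method that ignores between-patient variation would give. Dates of every event and of exit must be captured. The article does not say that the medical record already supplies them, but the planned time-to-event analysis already calls for event and exit dates.
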